### Questionnaire Instruments

In total, the effects of the intervention will be assessed with a 74-item questionnaire. The questionnaire contains items and inventories that can be classified into the following main categories: (1) demographics and background information, (2) observations of and exposure to ongoing bullying as well as more infrequent acts of bullying and harassment, (3) perceptions of bystander norms, trust in colleagues, and social climate, and (4) perceived behavioral control in the role as bystander.

The majority of the items are taken from established and validated indicators for assessing aspects of the workplace climate and workplace bullying, whereas some were developed for this project in order to fully capture perceived bystander norms and perceived behavioral control related to being a bystander in bullying situations. The items developed for this study is based on literature and/or suggestions from a reference group of specialists on the issue of workplace bullying and harassment. To date, there are no well-established measuring instruments for studying bystander norms and bystander behavioral control, hence such an instrument needed to be developed and tested for the present project. The developed scale has been psychometrically tested and validated in a pilot study of 70 elected health and safety representatives at the case company prior to the intervention project. The other scales have previously been validated in national and international studies.

#### Background Information and Demographics

Background and demographic factors that will be recorded in the survey include age, gender, educational level, position level (employee, manager with personnel responsibility, manager without personnel responsibility, labor union representative, health and safety representative), seniority, and if they have changed work teams during the last 3 months.

#### Bullying and Negative Acts

*Workplace Bullying-*Exposure to bullying behaviors from colleagues in the workplace is measured with the nine-item version of the *Negative Acts Questionnaire-Revised* (NAQ-R) inventory (Notelaers et al., 2018). NAQ-R describes negative and unwanted behaviors that may be perceived as bullying if occurring on a regular basis. All items are formulated in behavioral terms and focus on the mere exposure to inappropriate behaviors while at work with no references to the term bullying (Einarsen and Nielsen, 2015). The scale has proven reliable in former studies, calculating Cronbach’s Alpha for the nine-item version to be 0.86 (Einarsen et al., 2018). In addition, three items from the original version are included, as these three items addresses negative acts related to sexual behavior. Example items are “Spreading of gossip and rumors about you” and “Being shouted at or being the target of spontaneous anger or rage.” The respondents are asked to indicate how often they have been exposed to each specific item in the questionnaire at their present worksite during the last 6 months. Response categories range from 1 to 5 (“never,” “now and then,” “monthly,” “weekly,” and “daily”).

Observed bullying will be measured with the use of the *Bergen Bullying Indicator* (Einarsen and Raknes, 1991), a five-item instrument which measures the degree to which bullying is perceived to constitute a problem at the workplace (e.g., “Bullying at my workplace reduces our efficiency”). The scale has been used in former studies, which has reported Cronbach’s Alpha to be 0.93 (Hauan and Klaveness, 2018). A five-point Likert scale, ranging from totally agree to totally disagree, was applied.

*Observed and witnessed bullying* will also be measured with a single item; “Over the past 4 months, have you observed anyone being bullied in your team/department?”, accompanied by five answer alternatives with regard to frequency of experience (“No, never,” “Yes, a couple of times,” “Yes, every now and then,” “Yes, several times per week,” and “Yes, daily”).

The *observed bullying* question is followed by another question which measure whether or not the respondent intervened if (s)he observed bullying in her/his team. The response categories are as following: “Yes,” “no,” and “I have not observed any bullying activities.”

*Self-labeled victimization* from workplace bullying will be measured with a single item used in several previous studies on bullying (Olweus, 1991; Einarsen and Skogstad, 1996; Solberg and Olweus, 2003; Nielsen et al., 2011). The respondents are asked “*Have you been subjected to bullying at the workplace during the last* 4 *months?*” Response categories range from 1 to 5 (“no,” “rarely,” “now and then,” “once a week,” and “several times a week”).

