## Abstract

**Background:** Workplace bullying is an important and prevalent risk factors for health impairment, reduced workability and lowered efficiency among both targets and observers. Development and tests of effective organizational intervention strategies are therefore highly important. The present study describes the background, design, and protocol of a cluster randomized controlled trial evaluating the effectiveness of an organization-wide intervention on preventing workplace bullying with a focus on promoting active and constructive bystander behavior. The main overarching goal is to develop an easy to use and standardized organizational intervention based on theory and research in the role of bystanders in bullying situations with the potential of reducing the prevalence of workplace bullying. The theoretical framework of the study is theory of planned behavior (TPB; Ajzen, 1991).

**Methods/Design:** Using a full randomized control trial (RCT) design, this project will empirically test the outcomes of an intervention program targeting bullying and harassment as the main distal outcomes and perceived behavioral control and helping behavior among bystanders as the main proximal outcome. A 1-year cluster randomized controlled design will be utilized, in which controls will also receive the intervention. About 1,500 workers from two different locations of a Norwegian industrial company will be randomized into one intervention group and two control groups with at least 400 workers in each group. A survey will be conducted electronically. With a total of three assessments over 10–12 months, the time interval between the measurement times will be 4 months. Thus, the data collection will take place at baseline, completion of the intervention and at 4 months follow-up.

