### Study Design

This project has an RCT design that includes a range of departments from the case company, a Norwegian industry company. The company has two main locations, one on the west coast (location A) being the larger plant with some 1,600 employees and one in mid Norway (location B) being the smaller plant with some 800 employees. In location A, being the larger facility, all departments in the production part and two administrative departments will be randomly assigned to an intervention group and a control group. The control group will receive the intervention 6 months later, as will location B. As such, the location that is given the intervention last (location B) will also serve as an additional control group for the first interventions carried out in location A. Hence, we have two control groups for the initial intervention. In order to carry out a valid and reliable study of causal relationships and mechanisms, it is necessary to use a design where the study variables are measured repeatedly over time. In this project, we will use a mixed method design by combining a longitudinal survey, qualitative interviews, with this RCT design. All employees in the selected departments in the two locations of the case company will be invited to participate in a prospective questionnaire survey that will be distributed three times during a 12-month period. The questionnaire will be identical at all assessment points. It will be possible to distinguish between managers with personnel responsibility, managers without personnel responsibility, safety representatives, labor union representatives, other level employees, and the unit to which they belong. Data will be collected through *Surveyexact*, a web-based system for secure administration of questionnaires. The system is developed for the purpose of tracking individuals over time in a way that satisfies demands for anonymity and personal security and data protection. When accessing the web-based questionnaire by a link, the respondents will be asked to provide their informed consent before responding to the questionnaire. No personally identifiable information about respondents will be available to researchers, as data will be de-identified prior to analyses.

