### Sample

All employees in the intervention and control groups will be invited to participate in the three survey measurements. The total number of employees participating from both locations amounts to about 1,500. The surveys will be carried out approximately 4–6 months after intervention as well as 10–12 months, this to study the outcomes of the control groups who receive the intervention 6 months later and in order to study more long-term effects of the initial intervention.

Each employee in the company is provided with a smartphone when starting their employment. The survey will therefore be conducted electronically using these personal smartphones. The purpose of the survey will be to identify changes in the prevalence of bullying behavior, the social climate in the department, as well as the role played by bystanders in the working environment.

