### Statistical Power

In order to estimate sample size, we conducted a power analysis. One of the primary goals of power analyses is to estimate the number of respondents required in a study to minimize the likelihood of a false negative finding. In the context of intervention studies, the goal is to estimate the number of respondents per group to detect a difference between intervention and control groups. An *a priori* power analysis was conducted using G*Power 3.1.9.2 (Heinrich-Heine-University, Dusseldorf, Germany) with an alpha level of 0.05, power established at 0.80, and an effect size of 0.279. The optimal sample size calculated turned out to be 204 in each sample group (control and intervention group), yielding an optimal total sample size of 408. Based on previous survey studies from Norway in similar settings, the expected response rate is 55–70% at each of the measurement times. For the baseline measurement, the expected response rate will provide a sample size in the area of 750–1,050 respondents. Across all three time points, such a response rate will provide a sample size of about 190–515 respondents. Thus, the intervention study will strive for meeting the high end of the expected response rate of similar studies to meet the estimate from the power analysis and should have no problem in meeting sample sized from T1 to T2. The survey will be conducted electronically. With a total of three assessments over 10–12 months, the time interval between the measurement times will be 4 months.

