#### Recall Bias

As is common with questionnaire surveys asking about a person’s past experiences, there is a risk of recall bias. To minimize this risk, we have included a relatively short and specific time period for most items (last 4 months before the survey), and items have a relatively low level of abstraction and should therefore be likely to be associated with specific events. As bullying represents a violation of a person’s physical and psychological integrity, people are likely to remember such events.

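### The NAQ-R asks about 6 months while surveys are set 4 months apart, so at least a third of the T2 window predates the intervention; the article's conflicting T2 timings decide how much more

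*Protocol article*

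**What the plan says.** Bullying and Negative Acts describes nine NAQ-R items plus three added items on sexual behavior. Respondents report "how often they have been exposed to each specific item in the questionnaire at their present worksite during the last 6 months". Study Design says the questionnaire is the same at each wave, so this window applies at T1, T2 and T3. The single observed-bullying item and the self-labeled victimization item each ask about 4 months. Recall Bias says the survey uses "a relatively short and specific time period for most items (last 4 months before the survey").

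On timing:
- Statistical Power: "With a total of three assessments over 10–12 months, the time interval between the measurement times will be 4 months".
- Abstract: "the data collection will take place at baseline, completion of the intervention and at 4 months follow-up".
- Sample: "The surveys will be carried out approximately 4–6 months after intervention as well as 10–12 months".
- Study Design: "The control group will receive the intervention 6 months later, as will location B".

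Hypothesis 1.2, listed under a T1-to-T2 heading, predicts lower exposure to bullying behaviors in the intervention group. Hypothesis 3 expects the controls, treated after T2, to show the same pattern from T2 to T3. Objectives names harassment and bullying as the main distal outcomes.

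**The concern.** A respondent gives one answer for the whole recalled period. If part of that period lies before the intervention, the answer mixes untreated with treated time, and no later analysis can separate them. The window is the same in every group, so the effect is to shrink a true difference, not to create a false one. A null result on hypothesis 1.2 would then be hard to read: the program may not work, or the question may have reached back too far. According to Dissemination, the company will use the findings to decide on implementing the intervention throughout the organization. The overlap also means that two of the months reported at T2 were already reported at T1.

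**Working it through.** **1. The plan's own sample size.** Inputs from Statistical Power: effect size d = 0.279, alpha 0.05, power 0.80, 204 per group. Two-sided normal formula: n = 2 × (1.960 + 0.842)² / 0.279² ≈ 202 per group; the t-test version gives 203. The stated 204 is reproduced closely. A one-sided test would need about 160.

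**2. Minimum overlap.** The window is 6 months and the interval 4 months. The T2 window reaches 6 − 4 = 2 months before T1, so at least 2/6 = one third predates the intervention, more if group sessions run on after T1. Controls are treated after T2, so the T3 window likewise includes at least one third of untreated time for hypothesis 3.

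**3. The timeline.** Three waves 4 months apart span 2 × 4 = 8 months, not 10–12. Two equal intervals over 10–12 months would be 5–6 months each. A 5-month interval leaves at least 1/6 of the window before T1; a 6-month interval need leave none.

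**4. Illustrative size.** Let m be the months from intervention to T2. Assume the effect shrinks in proportion to the post-intervention share, d = 0.279 × m/6, and take power = Φ(d × √(204/2) − 1.96), without clustering.

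| m | Share after intervention | d | Power at 204 per group | n per group for 80% |
|---|---|---|---|---|
| 0 | 0 | 0 | about alpha | – |
| 2 | 33% | 0.093 | 15% | 1,815 |
| 3 | 50% | 0.140 | 29% | 807 |
| 4 | 67% | 0.186 | 47% | 454 |
| 5 | 83% | 0.233 | 65% | 291 |
| 6 | 100% | 0.279 | 80% | 202 |

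The 4–6 months given in Sample correspond to the last three rows. The completion wording in the Abstract corresponds to the first row or close to it. The 4-month interval caps m at 4.

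**5. Does a 4-month window cure it alone?** With d = 0.279 × m/4, power is 80% at m = 4, 56% at m = 3 and 29% at m = 2. At m = 0 the 4-month items also cover only untreated time. Both the window and the timing need fixing.

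**6. Recall Bias against the items.** Among bullying items with a stated window, 9 + 3 = 12 use 6 months and two use 4. The article gives no reason for the difference.

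**The case against.** The strongest reply is that the timeline is inconsistent and need not be read at its worst. If Sample governs, the pre-intervention share runs from one third down to zero, and a total span of 10–12 months with controls treated 6 months later fits waves nearer 5–6 months apart. That stands: the loss may be small. It stands only by setting aside the 4-month interval, which the article states in both the Abstract and Statistical Power.

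It is also fair that no instrument is ranked as the main bullying measure, that two bullying items already use 4 months, that 0.279 is not tied to the NAQ-R, and that answers are frequency categories in which recent months may weigh more. The shrinkage need not be linear. Lengthening or shortening the recall period of an established instrument is also a real trade-off.

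A reader might infer two stronger points that the article does not support. The first is that T2 exposure lies wholly before treatment. That requires T2 to coincide with the group sessions; at 4 months, two thirds of the window follows the intervention, and completion may mean the later follow-up session. The second is that the background item on "if they have changed work teams during the last 3 months" would miss moves between arms. Departments are randomized, so a team move within a department does not change arm, and Study Design says respondents can be distinguished by unit and tracked over time.

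**Conclusion.** The point holds as a mismatch between recall window and survey interval, made worse by contradictory timing. With waves 4 months apart, at least one third of the NAQ-R window at T2 precedes the intervention, which attenuates hypothesis 1.2 and, from T2 to T3, hypothesis 3. Under the Sample timing the pre-intervention share is one third to zero; under the Abstract's completion wording it is most or all of the window, and most of the 4-month windows too.

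The direction, toward no difference, needs only that a real effect begins with the intervention. The power figures (47%, 65% and 80% at 4, 5 and 6 months) also rest on linear dilution, an immediate effect, an effect size borrowed from a calculation that names no outcome, and no clustering. They are illustrations, not estimates. The stated 204 per group is not wrong on its own inputs. This should be fixed, but it affects one instrument among several and cannot produce a false positive.

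**What to change.** 1. Reconcile the Abstract, Study Design, Sample and Statistical Power into one timing for T2 and T3. Count it from the end of local roll-out, make it no shorter than the recall window, and check it against the stated delay before the control groups are treated.
2. Use one recall window for all exposure items at all waves, no longer than the time from intervention to survey. Four months, as in the two single items, would match the stated interval. If the 6-month window is kept, space the waves 6 months apart instead.
3. Correct the Recall Bias statement so that it describes the windows actually used.

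Shortening the window is a wording change if made before T1. Its cost is some loss of comparability with the instrument's usual form, which matters little for a contrast between groups answering the same questions. Keeping 6 months avoids that cost but gives up the 4-month interval; two 6-month intervals total 12 months, the upper end of the stated study span, before any allowance for roll-out time.
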